## Document Revision History

### Version

1. Protocol 1.0, July 1st, 2021

2. Protocol 2.0, September 1st, 2021

#### Revision in 4.1 Inclusion Criteria

Given the fact that a coronavirus disease 2019 (COVID-19) vaccine is now available to children ages 12 through 17 in China, “Aged 18 years or older” changed to “Aged 12 years or older”.

#### Revision in 5.1 Entering Screening

“A signed informed consent will be obtained from the subject or their legally authorized representative before any study-related procedures are undertaken” changed to “A signed informed consent, or proxy consent in the case of minors (aged < 18 years), will be obtained from the subjects, or parents/legal guardian of minors, or their legally authorized representative before any study-related procedures are undertaken. Under appropriate circumstances, minors should approach to provide assent by a member of the research team experienced with minors. The minor should personally write their name and date the assent form, which is then signed by the parent/legal representative and the researcher and copies retained/disseminated as for consent forms”

#### Revision in 5.6 Follow-Up

“The vaccination records of all participants, including doses, times and vaccine types, will be verified at the Month 3 visit by seeking data from the Health Code System which has a linkage to databases of routinely collected individual-level

vaccination information held by the Local Health Administrative Committee”  
added.

#### Revision in 10 Ethical Considerations

“Subjects must provide informed consent to participate in the trial” changed to  
“Consent from the patient, or proxy consent in the case of minors, should be  
obtained by a designated member of the research team prior to their participation in  
the trial, after a full explanation has been given of the intervention options”.

## ABBREVIATIONS

|          |                                                       |
|----------|-------------------------------------------------------|
| AE       | Adverse event                                         |
| BCVA     | Best corrected visual acuity                          |
| CFDA     | China Food and Drug Administration                    |
| COVID-19 | Coronavirus Disease 2019                              |
| CRF      | Case report form                                      |
| FFA      | Fluorescein fundus angiography                        |
| NEI      | National Eye Institute                                |
| OCT      | Optical coherence tomography                          |
| SUN      | Standardization of Uveitis Nomenclature Working Group |

# **1 Introduction**

## **1.1 Background**

### **Why do we need a vaccine for COVID-19?**

As the Coronavirus Disease 2019 (COVID-19) continues to affect and kill thousands of people around the world, politicians, health professionals and the public want to know how to get out of the blockade and begin to return to normal life. Without a vaccine against SARS-COV-2, the coronavirus that causes COVID-19, there is always a risk of new disease outbreaks. While rigorous testing, contact tracking, and isolation procedures will help control the spread of COVID-19, the only way to significantly reduce the threat is to immunize a large enough population against the virus (often known as herd immunity) so that the population cannot transmit it. To achieve this, it is estimated that about 60% of the population to be immune to the disease Everyone 18 years of age and older is now eligible to get a COVID-19 vaccination. Widespread vaccination is a critical tool to help stop the pandemic.

### **Do people with underlying medical conditions need a vaccine for COVID-19?**

Adults of any age with certain underlying diseases are at increased risk of developing serious diseases due to the virus that causes COVID-19. The COVID-19 vaccine is recommended and can be administrated in most people with underlying diseases. People with autoimmune conditions may receive a COVID-19 vaccine. However, we should be aware that no data are currently available for this population. People from this group were eligible for enrollment in some of the clinical trials. However, evidence for the timing of COVID-19 vaccination in patients with autoimmune disease is still lacking.

### **What is uveitis?**

Uveitis is one of several vision-threatening diseases. Originally, uveitis refers to a

collection of diseases characterized by intraocular inflammation that mainly affect the uvea, consisting of the iris, ciliary body and choroid. Uveitis also encompasses a range of entities involving inflammation of adjoining intraocular structures including the retina, vitreous and optic nerve. According to the major site of inflammation, uveitis can be anatomically classified into anterior uveitis (inflammation of the iris and anterior chamber), intermediate uveitis (inflammation of the ciliary body and vitreous body), posterior uveitis (inflammation of the vitreous body, retina, choroid or even the optic disk) and panuveitis (a diffuse inflammation from the anterior through the posterior segment of the eye).

Uveitis can also be classified into two categories, infectious or non-infectious, and the standard treatments for the two categories are largely different. Infectious uveitis can be caused by a localized or systemic infection with a definite pathogens, such as cytomegalovirus, herpes simplex virus (HSV), *Toxoplasma gondii*, *Treponema pallidum* and *Mycobacterium tuberculosis*, which requires anti-infection therapy. Non-infectious uveitis can be associated with systemic diseases including spondyloarthritis, Behçet's disease, Vogt-Koyanagi-Harada disease (VKH) and sarcoidosis. In addition, non-infectious uveitis may be confined to the eye with no apparent associated systemic diseases, such as sympathetic ophthalmia, birdshot chorioretinopathy, serpiginous choroiditis, or multiple evanescent white dot syndrome. Most non-infectious uveitis entities are presumed to be an immune-related disorder, usually termed as autoinflammatory or autoimmune disease, which means a self-directed pathological process. In clinical practice, these entities are primarily treated with immunosuppressive agents to suppress the autoinflammatory or autoimmune responses.

### **What is the concern on vaccination in uveitis?**

Having uveitis is currently not a contraindication (a medical reason to avoid) the vaccine. In fact, getting the vaccine when having uveitis may be especially important,

given the disease may confer a higher risk for COVID-19 or severe outcomes. However, it is possible that individuals could have an immune response to the COVID-19 vaccine. It remains unclear whether this immune response may significantly impact on the outcome of patients with uveitis. Furthermore, uveitis may also be a possible adverse side effect of some other vaccines. Given the fact that patients with uveitis are on immunosuppressants like steroids, methotrexate, or biologics, they may be on different disease status (active, inactive or remission), and they have different causes (infectious or non-infectious), it is unknown about the best timing of COVID-19 vaccination which can cause minimal adverse events on uveitis patients.

### **What is the key question of our study?**

In this study, we aim to initiate a pragmatic randomized trial to investigate whether there is significant difference in outcomes of patients with an inactive uveitis (active uveitis is considered not eligible for COVID-19 vaccination) between prompt initiation of COVID-19 vaccination and deferred initiation of COVID-19 vaccination until uveitis remission.

### **1.2 Benefits and Risks**

The risks to participants are minimal with randomizing COVID-19 vaccination recommendations as part of clinical care, as it is simply testing two different vaccination strategies. The primary potential risk will be uveitis relapse. However, uveitis relapse is common and can be properly treated, and relapse related visual loss can be adequately and timely prevented provided a close monitoring. To minimize potential risk, we will implement best medical judgment and treatment if any study endpoint event occurs to assure the safety of participants.

The potential for public health benefit from our aims to randomize COVID-19 vaccination recommendations is of importance, potentially to the benefit of future

COVID-19 vaccination recommendation and decision in patients with uveitis. This study would provide direct evidence and timely data to guide physician to give proper recommendations on COVID-19 vaccination for patients with uveitis.

## **2 Objectives**

### **2.1 Trial Objectives**

The objective is to test the difference in ocular and systemic outcomes between prompt initiation of COVID-19 vaccination and deferred initiation of COVID-19 vaccination in patients with uveitis.

### **2.2 Primary Objective**

To compare the time to symptomatic uveitis worsening between prompt and deferred vaccination strategies for patients with uveitis.

### **2.3 Secondary Objectives**

To compare vaccine accessibility, patient compliance, clinically-confirmed uveitis worsening, visual outcomes, treatment interruptions and initiation of step-up treatment, hospitalization, laboratory-confirmed COVID-19 between prompt and deferred vaccination strategies for patients with uveitis.

### **2.4 Safety Objectives**

To evaluate the systemic adverse events of the prompt versus deferred vaccination strategies for patients with uveitis.

### 3 Study Design

#### 3.1 Overall Design

This is a pragmatic, randomized clinical trial to test the difference in ocular and systemic outcomes between prompt initiation of COVID-19 vaccination and deferred initiation of COVID-19 vaccination in uveitis patients who have not yet been vaccinated and whose ocular disease maintains inactive but has not yet achieved complete remission.

Approximately 1314 eligible subjects will be randomized 1:1 (657 subjects per group) to receive one of two vaccination strategy recommendations. In the prompt vaccination arm, subjects will be recommended to get a prompt initiation of COVID-19 vaccination. In the deferred vaccination arm, subjects will be recommended to get the vaccination after uveitis remission (inactive disease for 3 months after discontinuing all treatments for eye disease). All participants will be followed up for 3 months since randomization. The primary outcome will be the difference in time to symptomatic uveitis worsening.

#### 3.2 Study Schematic

[figure not shown]

### **3.3 Study Timeline**

Expected time for trial start: July 2021

Expected completion time of enrollment: October 2021

Expected time for end of trial: January 2022

*The end of trial refers to the date of the last visit of the last subject to complete the study, or the date of receipt of the last data point from the last subject that is required for primary, secondary and/or exploratory analysis, as pre-specified in the protocol and/or the Statistical Analysis Plan, whichever is the later date.*

Expected completion time of primary analysis: May 2022

## 4 Eligibility Criteria

An important goal of pragmatic randomized trials is to provide relevant and generalizable information to guide clinical decision-making. As such, the inclusion and exclusion criteria of pragmatic trials is often more broad than those of traditional randomized controlled trials.

### 4.1 Inclusion Criteria

A subject will be eligible for study participation if she/he meets all of the following inclusion criteria:

- a. Aged 12 years or older
- b. Not yet vaccinated prior to the Screening.
- c. Diagnosed with any forms of uveitis in any eye.
- d. An **inactive disease** status (all the following criteria are met):
  - (1) **Anterior chamber cells of 0.5+ or less (See SUN criteria in Appendix I);**
  - (2) **Vitreous haze of 0.5+ or less (See NEI/SUN criteria in Appendix II);**
  - (3) **No active inflammatory choroidal or retinal vascular lesions.**

### 4.2 Exclusion Criteria

The presence of any of the following will exclude a subject from the study enrollment:

- a. Complete uveitis remission: Inactive disease for 3 months after discontinuing all treatments for eye disease.
- b. Any known vaccine contraindications according to manufactures' instructions:
  - (1) Individuals with a history of anaphylaxis to any component of the vaccine;
  - (2) Individuals with a body temperature over 38.5°C;
  - (3) Pregnancy.

- c. Any other condition which, in the opinion of the Investigator, would put the subject at risk by participation in the protocol.

#### **4.3 Re-screening of Patients**

Individuals that do not meet the above eligibility criteria may be re-screened a minimum of 2 weeks after the last screening visit.

## **5 Study Procedures**

### **5.1 Entering Screening**

Procedures for obtaining consent include explaining the patient's disease, prognosis, and options, introducing the aims and methods of this trial, discussing the risks and benefits of participation and addressing the patient's questions and concerns. Patients will be given at least 24 hours to consider taking part. The subject is assured that participation in this study is voluntary and he/she can withdraw at any time, without giving a reason. A signed informed consent, or proxy consent in the case of minors (aged < 18 years), will be obtained from the subjects, or parents/legal guardian of minors, or their legally authorized representative before any study-related procedures are undertaken. Under appropriate circumstances, minors should approach to provide assent by a member of the research team experienced with minors. The minor should personally write their name and date the assent form, which is then signed by the parent/legal representative and the researcher and copies retained/disseminated as for consent forms.

### **5.2 Eligibility Evaluation**

The eligibility evaluation will be performed at the Screening. For detailed inclusion/exclusion criteria see Section 4.

The Investigator will perform slit-lamp biomicroscopy, ophthalmoscopy and visual acuity on each candidate during the Screening. Other auxiliary examinations including fundus photography, optical coherence tomography (OCT) and fundus fluorescence angiography (FFA), may be performed at the Investigators' discretion according to the clinical needs to evaluate patient's ocular condition, and examination results or reports will be recorded on medical notes.

### **5.3 Randomization Assignment and Masking**

After eligibility has been determined, assignment of a randomization takes place at the Baseline visit. Only subjects who meet all of the inclusion criteria and none of the exclusion criteria are eligible for randomization into the treatment phase. Randomization will be designed to yield expected assignment ratio of 1:1 to the prompt vaccination strategy and the deferred vaccination strategy. Randomization list will have been generated by a Statistician using a computer and will be properly kept by a Designated Study Coordinator. Both this Statistician and the Designated Study Coordinator will have no involvement in other parts of the trial. The Investigator who is designated as the Primary Treating Ophthalmologist and is responsible for the management of the subject in this trial will telephone the Designated Study Coordinator to obtain patient assignment information. Throughout the trial, the randomization assignment will not be masked to the Primary Treating Ophthalmologist, but the Primary Treating Ophthalmologist will not have direct access to the randomization list. The randomization assignment will be masked to an adjudication committee who will independently determine the study endpoint events according to medical data, records and examination reports written by the Primary Treating Ophthalmologist, the attending doctor or the examining doctor. **These medical notes and data will be collected by a group of Study Coordinators who mask any randomization assignment information and submit these materials online to the adjudication committee.**

#### **5.4 Baseline Assessments**

The Baseline visit becomes time-point zero from which all other visit dates are calculated. The Screening and the Baseline can be performed on the same day. Considering the pragmatic study design, to ensure a rapid enrollment and data collection for a broad range of participants, baseline clinical characteristics and medical history can be either reported by patients or retrieved by means of a study site-specific query of the health record. Pre-specific baseline data include the date of

birth, gender, ethnic group, height, weight, presence of hypertension, diabetes, coronary heart disease, malignancies, type of uveitis (anterior, intermediate, posterior or panuveitis), specific uveitis diagnosis, affected eye (right, left or both), duration of uveitis, number of flares in the past 12 month, best corrected visual acuity logMAR score, and intraocular pressure.

## **5.5 Interventions**

Interventions will take place at the Baseline visit. The Primary Treating Ophthalmologist will provide the recommendation of COVID-19 vaccination to the subject according to randomization assignment. For those randomized to the prompt vaccination, subjects will be recommended to go to vaccination site and get COVID-19 vaccination as soon as possible. Our ophthalmologic clinic does not provide the vaccination service. We will only give the recommendation to patients. For those randomized to the deferred vaccination, subjects will be recommended to get COVID-19 vaccination after the remission of uveitis. **Remission is defined as an inactive disease for 3 months after discontinuing all treatments for eye disease.** At baseline, all patients will also be educated to immediately contact us by phone call once they experience any discomfort or have any new ocular symptoms of eye redness, eye pain, decreased vision, light sensitivity or fark, floating spots. We will ask questions as prespecified in **5.6 Follow-up** on the phone call.

## **5.6 Follow-Up**

Routine follow-up encounters will then occur every month. Participants will complete trial visits primarily by telephone calls from the call center. However, all participants will need to complete an in-person clinic visit on the end of three months since baseline.

On phone call, patients will be asked to answer the following predetermined questions according to their randomization assignment. **Module 1** will be subjected to those in

prompt vaccination group, and **Module 2** will be subjected to those in deferred vaccination group.

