### **Module 1**

Question 1: Do you think you have had a uveitis worsening or disease recurrence (relapse) in the past month?

Yes, no or uncertain. If yes, specify which eye and duration.

Question 2: Have you ever experienced newly occurred eye redness in the past month?

Yes, no or uncertain. If yes, specify which eye and duration.

Question 3: Have you ever experienced newly occurred eye pain in the past month?

Yes, no or uncertain. If yes, specify which eye and duration.

Question 4: Have you ever experienced new blurred vision or decreased vision in the past month?

Yes, no or uncertain. If yes, specify which eye and duration.

Question 5: Have you ever experienced newly occurred light sensitivity in the past month?

Yes, no or uncertain. If yes, specify which eye and duration.

Question 6: Have you ever had newly occurred dark, floating spots in your field of vision (floaters, specks or moving clouds in your vision) in the past month?

Yes, no or uncertain. If yes, specify which eye and duration.

Question 7: Have you ever experienced other ocular or systemic symptoms in the past month?

Yes, no or uncertain. If yes, specify where and duration.

Question 8: Have you already been received any dose of COVID-19 vaccination?

Yes or no. If no, jump to Question 14.

Question 9: Which COVID-19 vaccine did you get?

Sinovac (CoronaVac), Sinopharm, ZFSW Biologics Company, others (specifically), or uncertain.

Question 10: How many doses of COVID-19 vaccines have you already been received?

One, two, three or more (specific numbers).

Question 11: When did you get each dose of COVID-19 vaccines?

Participants will be asked to provide the specific date as far as possible.

Question 12: Have you finished all required doses of COVID-19 vaccines?

Yes or no. If the answer is no, continue on Question 13, otherwise finished.

Question 13: When do you plan to get the next vaccine?

Participants will be asked to provide the specific date as far as possible. If participants answer they no longer intend to get the next vaccine, specific reasons should be provided. Questions finished.

Question 14: Why did not you get vaccinated?

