## **Module 2**

Question 1: Do you think you have had a uveitis worsening or disease recurrence (relapse) in the past month?

Yes, no or uncertain. If yes, specify which eye and duration.

Question 2: Have you ever experienced newly occurred eye redness in the past month?

Yes, no or uncertain. If yes, specify which eye and duration.

Question 3: Have you ever experienced newly occurred eye pain in the past month?

Yes, no or uncertain. If yes, specify which eye and duration.

Question 4: Have you ever experienced new blurred vision or decreased vision in the past month?

Yes, no or uncertain. If yes, specify which eye and duration.

Question 5: Have you ever experienced newly occurred light sensitivity in the past month?

Yes, no or uncertain. If yes, specify which eye and duration.

Question 6: Have you ever had newly occurred dark, floating spots in your field of vision (floaters, specks or moving clouds in your vision) in the past month?

Yes, no or uncertain. If yes, specify which eye and duration.

Question 7: Have you ever experienced other ocular or systemic symptoms in the past month?

Yes, no or uncertain. If yes, specify where and duration.

Question 8: Have you been disease-free and discontinuing uveitis treatment for 3 months?

Yes or no. If yes, jump to Question 15.

Question 9: Have you already been received any dose of COVID-19 vaccination?

Yes or no. If no, participants will be recommended to keep away from getting vaccination at present and the conversation will be finished, otherwise continue on Question 10.

Question 10: Which COVID-19 vaccine did you get?

Sinovac (CoronaVac), Sinopharm, ZFSW Biologics Company, others (specifically), or uncertain.

Question 11: How many doses of COVID-19 vaccines have you already been received?

One, two, three or more (specific numbers).

Question 12: When did you get each dose of COVID-19 vaccines?

Participants will be asked to provide the specific date as far as possible.

Question 13: Have you finished all required doses of COVID-19 vaccines?

Yes or no. If the answer is no, continue on Question 14, otherwise finished.

Question 14: When do you plan to get the next vaccine?

Participants will be asked to provide their plan on specific date as far as possible. If participants answer they no longer intend to get the next vaccine, specific reasons should be provided. Questions finished.

Question 15: Have you already been received any dose of COVID-19 vaccination?

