## **5.7    Unscheduled Visits**

Participants will encounter at the clinic and have unscheduled visit for any reasons. They will be asked to answer questions in Module 1 or Module 2 according to their assignment. They will also undergo three mandatory assessments, including **best-corrected visual acuity testing, slit-lamp biomicroscopy and ophthalmoscopy**, and other examinations at investigator's discretion. For those with disease worsening, participants will receive best medical judgment and proper treatment for worsening of the ocular or systemic conditions.

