### 6.2 Primary Outcome

The primary outcome will be the time to symptomatic worsening over the course of 3 months of follow-up.

**Symptomatic worsening is defined if one of following newly onset symptoms occurs in at least one eye lasting for at least 2 days: eye redness, eye pain, decreased vision, light sensitivity or floaters.**

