# **3 Study Outcomes**

## **3.1 Primary Outcome**

An adjudication committee who are unaware of group assignment will independently determine each endpoint event according to telephone call records from the call center, medical data, records and examination reports written by the follow-up staff, the primary treating ophthalmologist, the attending doctor or the examining doctor. These medical notes and data will be collected by a group of Study Coordinators who mask any randomization assignment information and submit these materials to the adjudication committee.

The primary outcome will be the time to symptomatic worsening over the course of 3 months of follow-up.

Symptomatic worsening is defined if one of following newly onset symptoms occurs in at least one eye lasting for at least 2 days: eye redness, eye pain, decreased vision, light sensitivity or floaters.

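### The symptom answers behind the primary outcome are taken by callers who very probably know the arm, although the symptom questions are identical in both arms and could be asked on an arm-neutral form first

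*Supplement*

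**What the plan says.** **Outcome.** Protocol 6.2: "The primary outcome will be the time to symptomatic worsening over the course of 3 months of follow-up". The event is any one of five "newly onset symptoms occurs in at least one eye lasting for at least 2 days" (redness, pain, decreased vision, light sensitivity, floaters). No examination finding is needed.

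**Collection.** Protocol 5.6: "Participants will complete trial visits primarily by telephone calls from the call center". On these calls "patients will be asked to answer the following predetermined questions according to their randomization assignment". Unscheduled visits follow the same rule (5.7): "They will be asked to answer questions in Module 1 or Module 2 according to their assignment". The schedule in 5.10 also has the modules answered at Month 3, and 5.5 applies the 5.6 questions to calls that patients start themselves.

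**Modules.** Questions 1-7 have the same wording and order in both, for example "Question 2: Have you ever experienced newly occurred eye redness in the past month". Each is answered yes, no or uncertain, with location and duration if yes. The modules first part at Question 8, which in Module 2 reads "Question 8: Have you been disease-free and discontinuing uveitis treatment for 3 months" and in Module 1 asks about vaccination. Later in the call, unvaccinated prompt-arm patients are encouraged to be vaccinated, and unvaccinated deferred-arm patients not in remission are advised against it for now.

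**Masking.** The adjudication committee is the only role stated to be masked (Protocol 5.3 and 6.1, SAP 3.1 and 6). Under SAP 3.1 it "will independently determine each endpoint event according to telephone call records from the call center", together with medical records and examination reports. Study Coordinators mask assignment information before submission (Protocol 5.3, SAP 3.1).

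**The concern.** The endpoint is what the patient tells an interviewer. Whether a vague reply becomes a yes or an uncertain, whether a symptom counts as new, and what duration is written down are all settled during the call. The masked part of the process starts only after that.

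The trial's own text supplies an expectation that could colour those entries. Protocol 1.2 names relapse as the main potential risk, and SAP 4 hypothesises earlier events under prompt vaccination. A caller who shares this view may more readily record a borderline answer as positive in the prompt arm. That would push the hazard ratio above 1, the direction in which SAP 4 rejects the null hypothesis.

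An open-label pragmatic design explains why patients and treating ophthalmologists know the arm. It does not require the symptom interview to be unmasked, since the symptom questions do not depend on the arm.

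**Working it through.** **Step 1: follow one answer to adjudication.**

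| Stage | Who | Arm known? | Source |
|---|---|---|---|
| Symptom reported | Patient | Yes, open recommendation | Protocol 5.5 |
| Questions 1-7 asked, answer and duration recorded | Caller, or staff at the visit | Very probably: module chosen by arm, arm advice on the same call | Protocol 5.6, 5.7 |
| Assignment information masked | Study Coordinators | Not stated to be masked | Protocol 5.3, SAP 3.1 |
| Event determined | Adjudication committee | Masked | Protocol 6.1, SAP 3.1 |

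The second row is the gap. Nothing in that row needs the arm until Question 8.

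**Step 2: what a differential in recording would do.** The documents give no size for one, so this is an illustration.

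Inputs from SAP 5: 657 per arm, 0.90 event-free in the deferred arm, 15% dropout, two-sided 0.05. Decision rule from SAP 4: 95% CI for the hazard ratio wholly above 1. Follow-up from SAP 10: analysis stops at month 3. Assumptions: 0.90 and 15% both apply at 3 months, with exponential times (SAP 5 ties neither to a time point).

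The plan's sample size is roughly recovered with 0.90 at period 3, uniform accrual over 3 periods and follow-up to period 6. Freedman's formula gives 197 events. The mean event probability is 0.178, so 197/0.178 = 1107, and 1107/0.85 = 1302, against 1314 stated. Caller masking changes none of these inputs.

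Observed event probability by month 3 with dropout:
- λ = −ln(0.90)/3 = 0.0351 and η = −ln(0.85)/3 = 0.0542
- q = λ/(λ+η) × (1 − exp(−3(λ+η))) = 0.0924

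Suppose there is no true effect, but the hazard of a *recorded* event in the prompt arm is multiplied by r:
- Events: D = 657 × [q + 1 − (1−q)^r]
- P(CI wholly above 1) = 1 − Φ(1.96 − √D × ln(r)/2)

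| r | D | √D × ln(r)/2 | P(CI wholly above 1) |
|---|---|---|---|
| 1.00 | 121 | 0 | 2.5% |
| 1.10 | 127 | 0.537 | 7.7% |
| 1.20 | 133 | 1.051 | 18.2% |

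**Step 3: check on the absolute scale.** Take 558 per arm (657 × 0.85), a true 10% risk in both arms, and extra recorded events in the prompt arm only.
- +1 point: HR = ln(0.89)/ln(0.90) = 1.106, D = 558 × 0.21 = 117, probability 7.9%
- +2 points: HR = ln(0.88)/ln(0.90) = 1.213, D = 558 × 0.22 = 123, probability 18.7%

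With all 657 per arm the figures are 8.6% and 21%. For scale, the design effect is 10.0% against 1 − 0.90^1.5 = 14.6%, a gap of 4.6 points.

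**The case against.** **The questions are scripted and closed.** They are predetermined, worded alike in both arms, and provide for no discretionary probing. This stands, and it narrows the route for bias to how a scripted answer is recorded. It does not close it: yes against uncertain, new against old, and the stated duration are still entered by the caller.

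**The caller does not decide the endpoint.** A reader might infer that callers accept or reject the 2-day criterion. They do not. The masked committee makes that decision, but on answers already recorded.

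**Adjudicators are protected.** A reader might infer that the call records unmask the committee, because everything from Question 8 on reveals the arm. The documents do not support that: coordinators are to mask assignment information first, and nothing shows that this would miss those items. The plan simply does not say which parts of the call record are removed.

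**Caller knowledge is inferred.** No section says that callers know the arm. The inference is strong, given the choice of module and the advice on the same call, but it remains an inference.

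**Patients are unmasked anyway.** This stands in full. They can over-report, or disclose the arm, and a caller may remember it from the previous month. Masking the form reduces interviewer bias only.

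**Conclusion.** The point holds as a gap in masking at the stage where the primary outcome is elicited. It rests on three facts in the documents: a symptom-only endpoint, modules chosen by arm, and no masking of callers. It also rests on one close inference, that callers therefore know the arm.

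The 8% and 18% describe any differential recording, including that from patients who know their arm. It is tempting to read them as the false-claim rate that unmasked callers would cause, or that the fix would remove. The documents cannot separate the two sources, and the 10-20% excess is itself an assumption. What the figures do show is that a modest differential, 1 to 2 percentage points on a 10% risk, is enough to matter under the SAP 4 rule.

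This is an inexpensive improvement worth making. It does not show that the design is invalid.

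**What to change.** **Protocol 5.6 and 5.7.** Put Questions 1-7 on one common form that shows no arm. Complete and lock it in the eCRF before the arm-specific vaccination questions open. At Month 3 and at unscheduled visits, have it completed before the patient sees the unmasked ophthalmologist. Use the same order for calls that patients start.

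**SAP 3.1.** State that the call record sent to adjudicators for the primary endpoint is limited to the symptom items, Questions 1-6. Redact any mention of vaccination in free text, including Question 7, where post-vaccination complaints may appear. Keep the redacted medical records and examination reports in the package as already planned, since they can clarify an uncertain answer or a duration.

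**Cost.** A change of eCRF screen order and a few sentences in three sections. Sample size, vaccination advice and visit schedule are untouched. The benefit is partial: patients stay unmasked and may disclose their arm, and a caller may remember it from an earlier call.
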